## Abstract

**Aims:** This study aims to evaluate the additional effect of anodal transcranial direct current stimulation (a-tDCS) applied on dorsolateral pré-frontal cortex on training postural balance with the use of video games in the aged.

**Methods: **This is a blinded, randomized, controlled clinical trial protocol, with older people of both genders. Participants will be randomized into three training groups: Group 1 (videogame balance training), group 2 (videogame balance training associated with anodal tDCS), group 3 (videogame balance training associated with sham tDCS). The training will be carried out twice a week for four weeks, totaling eight sessions, and will be performed with the Nintendo Wii videogame console, using games that stimulate the postural balance associated with tDCS, with anode applied over the left dorsolateral prefrontal cortex and cathode on the contralateral supraorbital region at 2 mA for 20 minutes. The postural balance will be assessed using the Mini Test of the Balance Assessment System and posturography. Evaluations will be carried out before and after eight training sessions and 30 days after the end of treatment.

**Discussion:** Some studies show favorable results from the use of video games in improving postural balance in older people; however, their effect does not remain long-term. TDCS associated with other therapies can potentiate and prolong the effects of these therapies owing to its ability to stimulate neurotrophins important for neurogenesis, facilitating tasks that require attention, and helping to consolidate learning and memory. The effect of the two associated techniques on balance has not yet been tested in this population.

**Registration:** Brazilian Registry of Clinical Trials ID
U1111-1213-4266; registered on 15 October 2018.

## Introduction

Aging is a physiological occurrence that has several consequences, including an increased risk of falls
^1,
2^. The incidence of falls increases proportionally to age, from 28% to 35% in the older people over 65 years and from 32% to 42% in those over 75 years. Falls can lead to musculoskeletal injuries, and in more severe cases, they can lead to death
^1,
3,
4^.

Preventive therapies for the risk of falls can be performed with the use of technological resources, such as videogames. Studies using videogames have shown positive effects in improving the postural control, balance, and functional capacity of the older people when practiced regularly
^5^. They have been widely used by therapists with high acceptance in clinical practice because they are motivating, challenging, and recreational, showing good evidence to improve postural control in the older people
^6–
9^.

Another technique that has aroused interest in clinical practice is transcranial direct current stimulation (tDCS), which consists of low-intensity current, and can be applied to the scalp by means of rubber electrodes, thus promoting changes in the potential of resting membrane, such as depolarization by the anode electrode or hyperpolarization by the cathode; modulating cortical excitability
^10,
11^. Anodal tDCS, when applied over the long term, can stimulate the brain-derived neurotrophic factor (BDNF), which is an important protein for stimulating neuroplasticity, improving attention, consolidating learning, and memory. Thus, its use has aroused interest for the older people, in order to reduce cognitive and motor declines
^12–
15^.

However, the protocols for the use of tDCS associated with tasks that involve balance, in order to improve balance are not yet defined, and are being applied in different dosages and locations
^16–
18^, therefore, further studies are necessary to verify the benefit of tCDS in association with other therapies. For that reason, the primary objective of this study is to assess whether tDCS can enhance and prolong the effects of videogame training on improving postural balance in the older people. Secondarily, check if there is a relationship between the response to training and the quality of life. This study hypothesizes that the association of tDCS with virtual reality therapy is more effective in improving balance in the older people than therapy with videogames alone, and that the addition of tDCS will prolong the effects of balance training.

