### Sample size

The sample size was obtained using
G*Power 3.0.10 software, based on the outcomes from a pilot study. The calculation was carried out by the two-way repeated measures analysis of variance (ANOVA), considering the mean value (before and after training, and 30-day follow-up) for the control groups (25.46) active (27.46) and sham (24.66) and the pooled standard deviation (SD
_pooled_) (2.89), with α = 0.05, β = 0.2 (80% of power) and the effect size of 0.40. A total of 15 individuals were determined to be required for each group (total sample: 45 individuals). Considering possible dropouts and to ensure a sample size that will demonstrate the effect of the intervention, the sample will be expanded by 25%, resulting in 19 individuals in each group, thus totalling 54 participants.

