### Outcome assessments

All evaluations will be carried out on three occasions: pre-intervention, after eight treatment sessions and 30 days after the end of the training (follow-up). The training will be held twice a week, for 4 weeks, totalling 8 sessions.

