### Statistical analysis

All statistical tests will be performed using
SPSS (V22, IBM Corporation, New York, USA). Initially, we will perform the test of normality of the sample using the Shapiro-Wilk test, considering the significance level defined as a value of α < 0.05. The parametric data will be expressed as a mean ± SD (standard deviation), and the nonparametric data as a median (IQR); the categorical data will be described as absolute values and as a percentage of the total sample.

The variables of the data of the Mini-BESTest, Posturography, obtained pre-intervention, post-intervention and 30-day follow-up for the three groups (control, active and sham) will be calculated by the two-way repeated measures analysis of variance (ANOVA) for the parametric data and the Friedman’s test for the nonparametric data.

Finally, to verify whether there is a correlation between BESTest values and the symptoms of depression and quality of life, Pearson’s R correlation (parametric) or Spearman correlation (nonparametric) for the three groups in three evaluated times will be performed, verifying the degree of correlation (r) and its significance (p).

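### The primary objective claims that tDCS both enhances and prolongs the training effect, but the stated analysis does not separate the two

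*Protocol article*

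**What the plan says.** The Introduction gives a primary objective with two verbs: "the primary objective of this study is to assess whether tDCS can enhance and prolong the effects of videogame training on improving postural balance". The hypothesis repeats the split. It says first that the combination is more effective for balance than videogame therapy alone, "and that the addition of tDCS will prolong the effects of balance training".

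Under Outcome assessments, balance is measured "pre-intervention, after eight treatment sessions and 30 days after the end of the training (follow-up").

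Under Statistical analysis, the Mini-BESTest and posturography values "obtained pre-intervention, post-intervention and 30-day follow-up for the three groups (control, active and sham) will be calculated by the two-way repeated measures" analysis of variance, "for the parametric data and the Friedman’s test for the nonparametric data". No model term or contrast is tied to either verb, and *prolong* is not defined.

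The Sample size section uses one mean per group across the visits: "the mean value (before and after training, and 30-day follow-up) for the control groups (25.46) active (27.46) and sham (24.66"), with a pooled SD of 2.89, an effect size of 0.40 and 15 participants per group.

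**The concern.** *Enhance* and *prolong* are different quantities. The first is a larger gain by the end of training. The second, read as a claim separate from the first, is about how much of the gain survives afterwards. If anodal tDCS raises the gain and the gain then fades as it does in the other arms, the anodal arm is still ahead at 30 days, and both the group effect and the group-by-time term can be significant. Nothing about durability has then changed.

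At stake is half of the primary objective and the second clause of the hypothesis. Without a named comparison, a positive overall test could be reported as support for both parts. A real difference in retention with equal initial gains could also be missed.

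**Working it through.** **Inputs from the protocol article (Sample size):** group means 25.46, 27.46 and 24.66; pooled SD 2.89; f = 0.40; alpha 0.05; power 80%; 15 per group. Three visits (Outcome assessments).

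**Assumptions, not in the article:** equal SD at each visit; a common visit correlation ρ, set to 0.5 unless stated; the visit profiles in step 2.

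**1. Which test sets the sample size.** The grand mean is 77.58/3 = 25.86. The deviations are −0.40, 1.60 and −1.20, so the SD of the means is √((0.16 + 2.56 + 1.44)/3) = 1.178, and f = 1.178/2.89 = 0.407, in line with the stated 0.40. For the group main effect with m = 3 visits, λ = f²·N·m/(1 + (m−1)ρ) = 0.16 × 45 × 3/2 = 10.8 on 2 and 42 df, which gives power 0.817. N = 45 is thus reproduced as the group effect averaged over visits. With the same f and ρ, the interaction needs N = 18, the time effect N = 12, and a one-way ANOVA N = 66.

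**2. What the two ANOVA terms respond to.** Control and sham are identical in each profile, with 15 per group.
- Group: λ = n·m·Σ(group mean − grand mean)²/(SD²(1 + 2ρ)), on 2 and 42 df.
- Interaction: λ = n·Σ(interaction residual)²/(SD²(1 − ρ)), on 4 and 84 df.

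For profile A, the group means over visits are 23, 25 and 23. The group sum of squares is 2.667, so λ = 15 × 3 × 2.667/(8.352 × 2) = 7.18. The interaction sum of squares is 4.0, so λ = 15 × 4.0/(8.352 × 0.5) = 14.37.

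| Profile (pre/post/30 days) | Control and sham | Anodal | Points lost, anodal v others | Share of gain kept, anodal v others | Power, group | Power, interaction |
|---|---|---|---|---|---|---|
| A. Larger gain, same points lost | 22/24/23 | 22/27/26 | 1 v 1 | 80% v 50% | 63% | 85% |
| B. Larger gain, same share lost | 22/24/23 | 22/27/24.5 | 2.5 v 1 | 50% v 50% | 39% | 73% |
| C. Same gain, better kept | 22/24/22 | 22/24/24 | 0 v 2 | 100% v 0% | 11% | 47% |

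Profile B shows no prolongation on either measure of loss, yet anodal is 1.5 points higher at 30 days. Both tests reject more often there than in C, where prolongation is the only effect. The exact powers depend on the assumed profiles; what carries over is that both terms respond to the initial gain.

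**3. Friedman's test.** It ranks visits within participants. It does not compare groups, so it addresses neither verb as a between-arm claim.

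**4. Precision of the contrast that looks at loss.** For the anodal-minus-sham difference in change from post-training to 30 days, the half-width is 1.96 × 2.89 × √(2(1 − ρ)) × √(2/15):
- ρ = 0.5: 1.96 × 2.89 × 0.365 = 2.07 points
- ρ = 0.7: 1.96 × 2.24 × 0.365 = 1.60 points
- ρ = 0.84: 1.96 × 1.63 × 0.365 = 1.17 points

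The value 0.84 equals the reliability coefficient that the article quotes for the Mini-BESTest. It serves here only as an illustrative upper value. For scale, the anodal-minus-sham difference used for sizing, averaged over visits, is 27.46 − 24.66 = 2.80 points.

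**5. Why points lost cannot stand alone.** Suppose anodal gains 3 and keeps 80% (loses 0.6), while sham gains 1 and keeps 50% (loses 0.5). The change contrast favours sham by 0.1 point although anodal retained far more of its gain. The share retained has to be read beside it.

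**The case against.** The best defence is that this is a condensed article. Contrasts that follow a repeated measures ANOVA are commonly left to an analysis plan, and that plan is not shown. This has weight, and the absence of a contrast alone would not be a finding. What stands is that the article itself fixes a two-part primary objective and sizes the trial on a figure that reproduces as a visit-averaged group effect, which matches only one reading of that objective, and loosely.

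A second defence is that *prolong* may simply mean that benefit is still present later. A comparison at 30 days would then answer it. That reading is possible, since the Abstract says of earlier videogame studies "however, their effect does not remain long-term". But the objective and the hypothesis list prolongation apart from a stronger effect, which favours the other reading. Under either one, the term needs a named comparison.

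Three stronger readings are tempting and are not supported:
- *The trial cannot answer the question.* It can. Both post-training visits are scheduled, and the interaction contains the post-to-30-day component even though its omnibus test does not isolate it.
- *A significant ANOVA term will be declared proof of prolongation.* The article gives no such decision rule. The risk is an ambiguous result, not a stated misuse.
- *Thirty days is too short for a long-term claim.* The long-term wording is background about earlier studies. The objective makes no long-term claim, and the 30-day visit is stated openly.

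**Conclusion.** The point holds as a mismatch between a two-part primary objective and a single overall analysis. Under the assumed profiles (SD 2.89, ρ = 0.5, 15 per group), the stated ANOVA terms reject in 39% to 63% (group) and 73% to 85% (interaction) of trials when the anodal arm has a larger gain without a smaller loss in points. They reject in 11% and 47% when it has only better retention. Those percentages are illustrative: the article gives no expected gain, no visit-level means and no visit correlation. The conclusion that neither term isolates loss of the gain follows from the structure of the tests and does not rest on those figures.

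The defect lies in the stated objective and analysis, not in the data collected. It should be corrected because it bears on a primary claim and the correction is cheap.

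**What to change.** 1. **Enhance:** test the anodal v sham difference in Mini-BESTest change from pre-intervention to post-training.
2. **Prolong:** report, each with a 95% confidence interval, the anodal v sham difference in change (a) from post-training to 30 days and (b) from baseline to 30 days. Give the contrasts in 1 and 2 against the videogame-only group as well, because the hypothesis names that comparison.
3. **Wording of conclusions:** describe a 30-day difference alone as a benefit still present at 30 days. Claim slower loss only if contrast (a) supports it, read beside the share of the gain retained in each arm, since points lost penalise the arm with the larger gain.

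**Cost:** a change of wording and a few contrasts from visits already scheduled, with no new visit or participant. The drawback is precision. With 15 per group, contrast (a) has a half-width of about 2.1, 1.6 or 1.2 points at visit correlations of 0.5, 0.7 or 0.84, so the prolongation part may have to be presented as an estimate only.

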### Recruitment and allocation

Participants in this study will be community elders elected according to the criteria established for allocation. They will be randomized into 3 groups:

Group 1: Control Group (Video game balance training);

Group 2: Anodal group (Video game balance training associated with anodal tDCS);

Group 3: Sham Group (Video game balance training associated with sham tDCS).

A researcher not involved in evaluations or training will be responsible for allocating participants via
www.randomization.com.

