### Intervention procedures

***Video game Balance training***. The balance training sessions will be performed using only the video games in group 1 (control), group 2 will be the balance training with the video games associated with the anodal tDCS and group 3 will be the balance training with the video games associated with the sham tDCS. In this study, a control group was added that performed the same training as the other groups. However, using only the video game. The justification for this was to verify if only the balance training with video game is efficient and if the tDCS additional can potentiate the training results, making the outcomes more effective. The sham group was used to verify if the response to balance training with video game, can be influenced by some placebo effect.

Video game training will be carried out with the Nintendo Wii and Wii Fit Plus, placed in a slide projector to enlarge the image. The sequence of games will always be the same, and the participant should play an average of 5 to 7 minutes each game, passing the stage according to their learning.

The sessions will be held twice a week, for four weeks, totalling eight sessions. Each session will last 20 minutes. The selected games are table tilt, penguin slide and ski slalom, which will be performed standing on the Wii Board Balance and require movements that stimulate balance, such as the anterior, posterior and lateral tilt of the body, without moving (
Figure 1).

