### Blinding

The NeuroConn DC-STIMULATOR PLUS device has settings that allow the selection of the anodal stimulation or sham mode, by inserting codes. A researcher not involved in the procedures will program the equipment with the code to which the individual will be allocated. The stimulus mode will not be perceived by the external (supplementary functioning of the device, therefore, neither the researcher who will apply the intervention nor the individual will know what treatment will be applied (double-blind).

Participants in the group that will only perform training with video game will not be blind to treatment; however, a researcher will be responsible for the exclusive training of this group and will not be aware of the procedures with the tDCS of the other groups. All assessments will be made by researchers who have not participated in the training of the older people, and will, therefore, be blind to the intervention. A blinding questionnaire will be applied to guarantee its reliability and satisfaction with the treatment received (supplementary files 3 and 4), without the researcher knowing the training carried out by the participant.

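### The stated tDCS hypothesis is set against the unblinded, separately trained games-only arm; any claim for tDCS should rest on the double-blind anodal versus sham contrast already in the design

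*Protocol article*

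**What the plan says.** The hypothesis, at the end of the Introduction, is that tDCS combined with game training "is more effective in improving balance in the older people than therapy with videogames alone". The comparator it names is Group 1.

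Intervention procedures gives the arms matching roles. The games-only arm is there "to verify if only the balance training with video game is efficient" and to see whether adding tDCS strengthens the result. The sham arm is there to see whether a placebo effect influences the response to training.

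The Blinding section treats the arms differently:

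- **Games-only:** "Participants in the group that will only perform training with video game will not be blind to treatment", and "a researcher will be responsible for the exclusive training of this group".
- **Anodal and sham:** "neither the researcher who will apply the intervention nor the individual will know what treatment will be applied (double-blind").
- **Outcome assessment, all arms:** "All assessments will be made by researchers who have not participated in the training of the older people".

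Under Statistical analysis, the Mini-BESTest and posturography data "for the three groups (control, active and sham) will be calculated by the two-way repeated measures analysis of variance". Under Sample size, the trial is sized on the same type of analysis.

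**The concern.** The comparison that the hypothesis names differs from the anodal arm in at least three ways: the current, the participant's knowledge of receiving a device treatment, and the person who trains them. The trainer is completely tied to the arm, so no analysis of the games-only contrast can separate trainer from tDCS.

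The Mini-BESTest is a performance test scored on the best of up to three attempts, so effort and coaching can move it even when the assessor is blind. An analysis that followed the hypothesis literally could credit tDCS with an expectation or trainer effect.

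A related problem affects the stated purpose of the games-only arm. All three arms train, so none shows what would happen without training. Participants are also selected for a low score on the scale that serves as the primary outcome. A rise from before to after training in Group 1 therefore cannot verify that game training works.

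**Working it through.** **1. What each contrast contains**

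| Contrast | tDCS current | Expectation and device contact | Trainer |
|---|---|---|---|
| Anodal minus games-only | differs | differs | differs, tied to arm |
| Anodal minus sham | differs | alike if blinding holds | blind to allocation |
| Sham minus games-only | alike, apart from the 30-second sham current | differs | differs, tied to arm |

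Only the second row isolates tDCS.

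**2. Reproducing the plan's sample size**

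Inputs from Sample size: means 25.46 (control), 27.46 (active) and 24.66 (sham), SD 2.89, alpha 0.05, power 80%, effect size 0.40.

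- Grand mean = (25.46 + 27.46 + 24.66)/3 = 25.86. SD of the three means = 1.178. f = 1.178/2.89 = 0.407, against 0.40 stated.
- Between-group F with m = 3 visits: λ = f²·N·m/(1 + (m − 1)ρ), df (2, N − 3). The within-person correlation ρ is not stated; I assume 0.5.
- f = 0.40 and N = 45: λ = 0.16 × 45 × 3/2 = 10.8, power 0.817. This matches the stated 45. (At f = 0.40, ρ = 0.3 would need 36 and ρ = 0.7 would need 54.)

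So 45 is the size for a three-group omnibus test.

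**3. That test when tDCS does nothing**

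Suppose anodal and sham are equal and both lie 2.0 points above games-only on the mean over visits. The shift is illustrative; it equals the pilot active minus control difference, 27.46 − 25.46.

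- SD of the means (0, 2, 2) = 0.943; f = 0.943/2.89 = 0.326.
- N = 45, ρ = 0.5: λ = 0.326² × 45 × 1.5 = 7.18, rejection probability 63%.
- N = 45, ρ = 1: λ = 0.326² × 45 = 4.79, rejection probability 46%.

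**4. Power of the two contrasts at 15 per arm**

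Noncentral t, two-sided alpha 0.05. Baseline adjustment multiplies the SD by √(1 − r²), where r is the assumed correlation of baseline with outcome.

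| r | Anodal − sham, 27.46 − 24.66 = 2.80 | Anodal − games-only, 2.00 |
|---|---|---|
| 0 (unadjusted) | 73% | 45% |
| 0.3 | 77% | 48% |
| 0.5 | 84% | 56% |
| 0.7 | 95% | 73% |

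At 19 per arm, unadjusted, the figures are 83% and 55%.

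**5. Regression to the mean in the training-alone claim**

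Inputs: entry at Mini-BESTest 25 or below (Eligibility criteria), ICC 0.84 (Primary outcomes), SD 2.89 (Sample size, assumed to apply to the screened population). The population mean μ is not given.

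Expected spurious gain = (1 − 0.84) × 2.89 × φ(z)/Φ(z), with z = (25.5 − μ)/2.89.

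| Assumed μ | 22 | 23 | 24.66 | 25.46 | 25.86 |
|---|---|---|---|---|---|
| Gain, points | 0.10 | 0.16 | 0.29 | 0.36 | 0.41 |

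The last three are pilot means (sham, control and the grand mean), which include post-training scores and so may sit above the screening mean. That is why the range must extend downwards. Practice on the test would add to these figures.

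**The case against.** The strongest objection is that the design already protects against this. There is a randomised sham arm with the same electrode positions and a blinded operator, assessors are blinded in all arms, and a blinding questionnaire is planned. A reader might infer from the hypothesis that a positive trial could not be attributed to tDCS at all. The document does not support that: anodal versus sham can support attribution if it is the contrast relied on. Nor does the article call the hypothesis confirmatory or say that sham will be ignored; the aim and primary objective name no comparator arm. This stands, and it limits the point to the stated comparator and arm roles.

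Second, any three-group F can be significant through any pair, and follow-up contrasts may sit in an analysis plan that is not shown. This also stands. Their absence is not the criticism, and step 3 shows only that the omnibus result cannot carry the tDCS claim by itself.

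Third, regression to the mean and practice affect all randomised arms alike in expectation, so they do not bias a tDCS contrast. That is correct. They matter only for the claim that training alone works.

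What the objection does not remove is the wording itself. The hypothesis and the arm roles both point to games alone as the yardstick for tDCS, and a faithful analysis plan would follow them. Blinded assessors do not remove expectation or trainer effects.

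**Conclusion.** The point holds in a limited form. The article rests the tDCS hypothesis on a contrast confounded with expectation and trainer, while the contrast that can support attribution is present but cast as a placebo check. The size of the confounding cannot be estimated from the design. Any such effect passes in full into anodal minus games-only. If it were 2.0 points, with no tDCS effect, the omnibus test would reject 46% to 63% of the time at N = 45.

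On the pilot differences, anodal versus sham is also the better powered contrast: 73% to 95% at 15 per arm for r from 0 to 0.7, against 45% to 73% for anodal versus games-only. It reaches the planned 80% at 15 per arm only with a useful baseline correlation; the 84% figure holds at r = 0.5. These figures take the pilot means and SD at face value.

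The training-alone claim is not supportable. The part due to regression to the mean is modest, of the order of 0.1 to 0.4 points depending on the unstated population mean, but without an untrained arm it cannot be separated from a training effect.

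**What to change.** - **Hypothesis (Introduction) and arm roles (Intervention procedures):** state that any claim that tDCS enhances or prolongs the effect of training rests on anodal (Group 2) minus sham (Group 3) on the Mini-BESTest, preferably adjusted for baseline.
- **Contrasts with Group 1:** report them as supportive, labelled unblinded and trainer-confounded.
- **Training alone:** replace the aim of verifying that game training is efficient with a description of change under training, with no efficacy claim.

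No participants or staff are added. The costs are that the games-only comparison becomes supportive and that, because the Trial status section says collection is under way, the change must be documented as a dated amendment. Unadjusted power for the deciding contrast is 73% at 15 per arm, below the planned 80%, which is the practical reason to prefer baseline adjustment.
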